## Abstract

**Introduction:**

Lumbar radicular syndrome (LRS) can be a painful and debilitating condition. The optimum management strategies and their timing remain elusive despite extensive research. Surgery provides good short-term outcomes but has concomitant risks and costs. Physiotherapy is commonly practised for patients with LRS but its effects remain equivocal and there is a lack of consensus on the type, duration and timing of physiotherapy intervention. There is a lack of high-quality evidence into new and innovative management strategies and the timings of those strategies for LRS. This pilot trial is an essential preliminary to a definitive randomised controlled trial (RCT) assessing the effectiveness and cost-effectiveness of early physiotherapy intervention for patients with LRS. The study will test the protocol, the intervention, the use of outcome measures and the ability to set-up and run the trial to enable refinement of a future definitive RCT.

**Methods and analysis:**

This is a mixed-methods study encompassing an external pilot RCT with integrated qualitative interviews with patients, clinicians and other key stakeholders. 80 patients will be recruited from primary care and randomised, after consent into 1 of 2 groups. Both groups will receive individually tailored, goal orientated physiotherapy. The usual care group will begin their physiotherapy 6 weeks after randomisation and the intervention group at 2 weeks after randomisation. Outcome measures will primarily be feasibility parameters including the ability to recruit and retain patients and to deliver the intervention. Data will be collected at baseline, and 6, 12 and 26 weeks following randomisation.

**Ethics and dissemination:**

The study has received favourable ethical review from the East of Scotland Research Ethics Service (EoSRES) on the 20 August 2015 (15/ES/0130). Recruitment began on the 1 March 2016 and is expected to close in January 2017. Data collection is anticipated to be complete in July 2017. The study results will be made available to participants, clinicians involved in the study and the wider clinical community through publication in a peer reviewed journal and at conference presentations.

**Trial registration number:**

ISRCTN: 25018352, Pre-results; Clinical Trials.Gov: NCT02618278 Document version V1.1 23.9.2016.

Strengths and limitations of this studyThis feasibility study will inform the design and conduct of a definitive randomised controlled trial of an early physiotherapy intervention for the treatment of lumbar radicular syndrome (LRS).The intervention is a safer, cheaper alternative to surgery for patients with LRS and should be easy to adopt and deliver within current treatment pathways.The qualitative component of the study will enable patient and stakeholder views to be taken into consideration and they will be used to inform modifications to the intervention and design of the definitive trial.Recruitment in the feasibility study will be from 14 General Practitioner (G.P) practices in the north of England with diverse demographic populations. Generalisability of the results will need to be considered when planning a larger trial including other areas of the UK.

## Introduction

Lumbar radicular syndrome (LRS) is a painful and often disabling condition, which is usually of benign causation. It can be self-limiting and may last a short time with no significant sequelae or, in some individuals it can be severely painful and disabling in the long term. The reasons for the wide variations in presentation, outcome and duration in patients are not fully understood.^1^

LRS is perhaps better known as sciatica, although sciatica does not encompass neural dysfunction from the upper lumbar nerve roots and thus, the term LRS is preferred. LRS is defined as leg pain in an area served by one or more spinal nerve roots and can be accompanied by neurological deficit such as paraesthesia, anaesthesia and myotomal weakness.^2^ There are many and varied estimates of prevalence of LRS ranging from 1% to 43%.^3^

LRS is a major cause of disability, work loss and presentation to healthcare.^4^ The Health Council of the Netherlands estimated a cost of 2.9 billion Guilders to the Dutch economy in 1999 (around €1.5 billion at September 2015 exchange rate). The costs of surgery for LRS (microdiscectomy and laminectomy) were found to add $5 billion to the overall cost of back pain and LRS in the USA in 2004.^5^ The cost of physiotherapy for a group of patients who went on to have surgery for LRS accounted for 11% of the total preoperative costs or on average $379 per patient. The mean cost of imaging alone accounted for 31% of costs or $1067 for each patient,^6^ illustrating the relatively small costs of physiotherapy compared with other, non-therapeutic costs.

The management of LRS is a much debated and contentious area. Surgery for patients with LRS has been advocated, with good reported outcome.^7^ However, significant number of patients never have any substantial relief from surgery,^8^
^9^ with unsatisfactory outcomes in over 20% of patients at 5 years, irrespective of the type of treatment they receive, including surgery.^10^ Although, it is not known with any certainty how long to wait to allow spontaneous resorption of the inter vertebral disc (IVD) prolapse, it has been suggested that by 12 weeks 75% of LRS sufferers will have symptomatically resolved.^11^ The favourable effects of conservative treatment for LRS have been demonstrated with 90% of patients improving within 12 weeks after onset.^12^ A ‘wait and see’ approach is often advocated but a significant number of people suffering with LRS do not recover in the short or medium term and the optimal window for surgery can then be missed. Lewis *et al*^13^ note the importance of early treatment in order to prevent chronic symptom development and the ensuing resistance to treatment and costs.

While physiotherapy for LRS has been advocated, there is a lack of consensus on the type, duration or timing of intervention.^14^ There are numerous physiotherapy approaches to low back pain (LBP) and LRS, none of which have significant degree of scientific rigour surrounding them.

It is known that patients prefer and have improved outcomes with early intervention physiotherapy for LBP.^15–17^ Delayed initiation of physiotherapy for patients with LBP in primary care is associated with increased cost and increased healthcare consumption.^18^ These findings were echoed by Gellhorn^19^ who found that patients who received physiotherapy <4 weeks after onset of their LBP had lower healthcare usage (and associated costs) than those who received physiotherapy more than 3 months after onset. Although such evidence does not directly exist for the provision of physiotherapy for patients with LRS, it may be suggested that early intervention is preferable.

### Aims and objectives

The overall aim for the study is to investigate the feasibility of undertaking a fully powered, multicentre randomised controlled trial (RCT) to determine the effectiveness and cost-effectiveness of early intervention physiotherapy for patients with LRS.

### Objectives

The objectives of the pilot trial fall into two categories. First, process objectives will allow the analysis of the practical and logistical aspects of setting up and running the study. Second, the feasibility objectives will provide data on recruitment, the use of outcome measures, randomisation and data collection and the delivery of the training and intervention. This information will be used to inform the definitive RCT.

### Process objectives

To test the feasibility, practicality, safety and acceptability of the study design and protocol.Demonstrate the ability to set-up and recruit in primary care centres.To assess the feasibility of delivering the early intervention within the time parameters (2 weeks for the intervention group, 6 weeks for the usual care group).Demonstrate a recruitment rate of seven patients per month in a maximum of 14 G.P centres, equal to a rate of 0.5 of a participant per centre, per month.Demonstrate the ability to organise 75% of physiotherapy appointments within 2 weeks of randomisation.Patient attendance at 66% of individual sessions.75% of patients randomised to early intervention have their first session within 20 days of randomisation.Patient attrition rate of <25% over the course of the study.Outcome measurement return rate of 80% at 6/52 follow-up.

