### Primary and secondary outcome measures

The primary outcome measures for the study will evaluate the feasibility of a range of factors. These will include the recruitment of patients into the study in a timely manner, in particular the ability to identify eligible patients and their willingness to be randomised. The recruitment rate and initiation of treatment within 2 weeks for intervention arm and 6 weeks for usual care arm will be noted. Ensuring patient safety and acceptability of the intervention to patients and clinicians and acceptability of the trial protocol. The practicalities of providing the physiotherapy and patient adherence to the intervention and in addition, the number of patients being referred into the secondary care system will be noted and costed accordingly. The number of patients undergoing surgery for their LRS will be recorded and costed as will the number of adverse events (AE) and serious adverse events (SAE). Finally, the time taken from randomisation to physiotherapy treatment initiation will also be recorded.

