## Discussion

There is a lack of high-quality evidence about the optimal way to treat patients with LRS. This study is a preliminary step towards establishing if a novel physiotherapy intervention, delivered within 2 weeks of referral from the G.P is an effective treatment for these patients. This study has been designed to assess the feasibility of a future, full-scale trial and will not investigate effectiveness of the intervention. The definitive RCT will be informed by the results of the study and will investigate the effectiveness and cost-effectiveness of the intervention, with the potential for patients to have better outcomes with avoidance of surgery and long-term problems.

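### The early-arm start criterion allows 20 days although the arm is defined by 2 weeks, and the 2-week appointment criterion names neither an arm nor the first appointment

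*Protocol article*

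**What the plan says.** The abstract (Methods and analysis) defines the arms by start time: "The usual care group will begin their physiotherapy 6 weeks after randomisation and the intervention group at 2 weeks after randomisation". The Process objectives repeat these time parameters: "2 weeks for the intervention group, 6 weeks for the usual care group". Primary and secondary outcome measures uses the same pair: "initiation of treatment within 2 weeks for intervention arm and 6 weeks for usual care arm will be noted".

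Two numeric criteria for the start of treatment then stand in the same list of process objectives:

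- "Demonstrate the ability to organise 75% of physiotherapy appointments within 2 weeks of randomisation"
- "75% of patients randomised to early intervention have their first session within 20 days of randomisation"

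The Randomisation section says that both groups are treated under a common framework. Trial organisation and management gives timing as the only thing the intervention alters. The Data analysis plan will summarise time from randomisation to the start of physiotherapy by group, and will use the feasibility results to decide whether a definitive trial is feasible.

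The Discussion uses a different starting point for the clock: "delivered within 2 weeks of referral from the G.P".

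**The concern.** Start time is the whole experimental contrast, so whether the early start can be delivered is a central question for this pilot. The criteria that should answer it do not line up with the definition. The arm and the outcome use 2 weeks, while the criterion that names the early arm uses 20 days without explanation. The criterion that does use 2 weeks leaves its denominator open: it does not say which arm, which appointment, or whether a booking or an attended session counts.

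Two careful readers could therefore take identical data and disagree on whether the early start was achieved. That judgement feeds the decision on the definitive trial.

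**Working it through.** The article derives none of these thresholds by formula, so there is no stated figure to reproduce. The check is whether the criteria can hold together.

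**Inputs**

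- Early start: 2 weeks = 14 days; usual-care start: 6 weeks = 42 days (abstract; Process objectives).
- Early-arm criterion: 75% by day 20. Appointment criterion: 75% by day 14 (both Process objectives).
- Sample size: 80 (abstract; Qualitative).
- Allocation: 1:1, so 40 per arm. This is an assumption. The ratio is not stated for the 80, although Sample size cites a recommendation with equal groups of 35.
- Sessions: up to six over 8 weeks in both arms (The intervention).

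**The 20-day limit against the 2-week definition**

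- Excess over the definition: 20 − 14 = 6 days, and 6/14 = 43%.
- First sessions all held on days 15 to 20 would satisfy this criterion with none inside 2 weeks.
- Planned separation between arms: 42 − 14 = 28 days. With an early start at day 20: 42 − 20 = 22 days. Loss: 6/28 = 21%.

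**The 75% appointment criterion under its possible readings**

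| Reading | Needed | Most that is possible | Reachable? |
|---|---|---|---|
| First sessions held, both arms, usual care starting at day 42 | 0.75 × 80 = 60 | 40 of 80 = 50% | No |
| First sessions held, early arm only | 0.75 × 40 = 30 | 40 of 40 | Yes |
| Bookings made by day 14, whatever the session date | 0.75 × 80 = 60 | 80 of 80 | Yes |

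In the first row, reaching 60 would take 60 − 40 = 20 of the 40 usual-care patients (50%) starting within 2 weeks. The ceiling is simply the early arm's share of the patients, so it moves with the allocation ratio. It would reach 75% only if 60 of the 80 were in the early arm.

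If every session counts rather than the first, the criterion is harder even in the early arm. A patient who starts on day 14 and has five further sessions on later days has 1 of 6 (17%) inside the window.

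**The two criteria together**

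- If the 2-week criterion means early-arm first sessions held, 75% by day 14 guarantees 75% by day 20, and the 20-day criterion adds nothing.
- If it means bookings made, no percentage criterion tests whether treatment starts within 2 weeks, which is the start named in the outcome section.

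**The clock**

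Under Recruitment and consent and Randomisation, the patient contacts the team, is screened, consents in person and gives baseline data before being randomised. Two weeks from referral and two weeks from randomisation are therefore different intervals, and the article states no limit on the gap between them.

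**The case against.** The best defence is that the two criteria measure different things. One concerns organising appointments, which is a matter of service capacity. The other concerns the first session taking place. Booking within 14 days and attending within 20 can both be true, and a nominal start at 2 weeks needs some slack for rescheduling. This is plausible, and it is why the pair is not a proven contradiction. But the article never calls 20 days a tolerance, and its own outcome section judges initiation against 2 weeks.

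Two stronger readings are tempting, and the document supports neither.

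- A reader might infer that the pilot could succeed with nobody treated within 2 weeks. That holds only for the 20-day criterion in isolation. If the 2-week criterion counts early-arm sessions held, it would prevent such an outcome.
- A reader might infer that the 75% appointment criterion is impossible. That needs sessions held, both arms, an assumed allocation ratio, and usual care starting at 6 weeks. The outcome section could also be read as usual care starting within 6 weeks, which would loosen the ceiling. Leaving out the arm is probably an oversight.

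No single reading produces both harms.

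The lack of a percentage target for the usual-care start is not an error. That start is recorded, and the Data analysis plan summarises it by group. The Discussion's referral wording is descriptive and no criterion depends on it. Finally, the article states no pass/fail rule, the analysis is mainly descriptive, and actual start times will be reported whichever threshold is used. This limits the damage but does not make the thresholds consistent.

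**Conclusion.** The criteria for treatment start do not match the stated definition of the early arm and should be corrected.

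- **Window.** The early-arm criterion runs 6 days (43%) past the 2-week definition with no stated reason. If early patients started at that limit and usual care on day 42, the separation would be 22 days instead of 28. This is a boundary case, not a forecast.
- **Denominator.** The 2-week criterion has a ceiling of about 50% or is fully reachable, depending on a reading that the article does not settle. The 50% figure rests on 1:1 allocation, usual care starting at 6 weeks, and counting first sessions held across both arms.
- **Clock.** The Discussion's reference to GP referral is a minor inconsistency of wording.

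This is a defect in how stated thresholds are fixed. It does not threaten the pilot as a whole, because the underlying start times are recorded and will be reported.

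**What to change.** 1. Limit the 2-week criterion to first appointments of patients randomised to the early arm. With 40 in that arm (assumed), the target becomes 30 of 40.
2. Say whether it counts bookings made or sessions held.
3. Reconcile 2 weeks with 20 days so that the arm definition, the outcome and the criterion agree. If 20 days is meant as a tolerance, say so. Which window applies is for the trial team.
4. Judge delivery from the recorded times between randomisation and start, and report the between-arm difference in days beside the percentages.
5. Align the Discussion's description with the randomisation clock.

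The cost is mainly wording, and no new data field is needed. Recruitment began on 1 March 2016 and this version is dated 23 September 2016, so the change would be made during the trial. It should be dated, agreed by the trial management group, submitted as an amendment if required, and settled before start times are summarised by arm.

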### Feasibility objectives

To determine the acceptability of the intervention to patients and clinicians.Demonstrate acceptability of the primary and secondary outcome measures to patients and clinicians.To inform the sample size calculation for the definitive trial.

## Methods

### Design

Mixed-methods study comprising an external pilot RCT augmented by semistructured interviews with key stakeholders.

### Quantitative

Recruitment will occur in three, 20-week cycles, illustrated in table 1. In each of the three cycles there will be 12 weeks of active recruitment followed by up to 8 weeks for treatment to be completed. A 2-week period between cycles will provide time to reflect and analyse on the results from the stakeholder interviews and other feedback.

**Table 1 BMJOPEN2016014422TB1:** Recruitment cycles

[figure not shown]

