### The intervention

The goal-orientated physiotherapy regimen for both groups will be tailored to the individuals' requirements. Participants will be assessed using a biopsychosocial approach based on seven different elements; neurological dysfunction,^22^ motor control of movement of the lumbar spine and pelvis,^23^
^24^ movement restriction in the lumbar spine and pelvis,^25^ psychological barriers to recovery^26–28^ advice and education^29^
^30^ functional-based exercise^31^ and pain.^32^ Participants will receive up to six sessions of physiotherapy over an 8-week period or until they have achieved their predetermined goals.

The seven elements of assessment and treatment are neither exclusive nor exhaustive but reflect the complexity of the clinical reality of a patient presenting with LRS. The Medical Research Council (MRC) guidance for developing and evaluating complex interventions has, therefore, been adopted as the principal framework around which the study has been based.^33^

Implementation fidelity testing will be carried out in order to assess the treating clinicians are delivering what is intended by the protocol.^34^ An independent assessor will review video footage of physiotherapist and participant session in order to assess implementation fidelity.

Patients are allowed to withdraw from treatment at any point and this will have no detrimental effects on their ongoing healthcare.

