### Data analysis plan

As the trial is a pragmatic parallel group RCT, data will be reported and presented according to the CONSORT statement.^35^ The statistical analyses will be performed on an intention-to-treat basis. As a feasibility study, the main analysis will be mainly descriptive and will focus on CI estimation and not formal hypothesis testing. We will report rates of consent, recruitment and follow-up by centre and by randomised group. Outcome measures will be summarised overall and by randomised group. We will use the data from this feasibility study to estimate the consent rate, attrition rate, and the variability of the continuous outcomes (eg, leg and back pain VAS, ODI, EQ-5D) in the trial population and use this information to inform the sample size calculation for the definitive RCT. Since the intervention is therapist led we shall also use the data to estimate the intra-cluster correlation (ICC). We will also include, as part of the feasibility analysis, estimation of the effect size for the 12-week VAS-pain outcome (the probable primary end point for the definitive study) with CI estimates to check that the likely effect is within a clinically relevant range (as confirmation that it is worth progressing with the full trial). This information along with the acceptability of the study design and protocol to patients, therapists and G.Ps; the safety of the intervention; patient recruitment and consent/retention rates will enable us to determine whether or not the definitive RCT is feasible, within a satisfactory timescale and cost envelope using the UK centres alone. The time from randomisation to start of physiotherapy will be summarised by randomised group.

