### Qualitative analysis

The constant comparative method will be used for the analysis of the interview data.^36^ A preliminary thematic analysis^37^ will be undertaken after three interviews by the lead author. This will take the form of category generation by defining units of data code generated by the interviews. Category generation will draw on both the interview data from the interviewee as well as the notes and reflections of the interviewer. The former aims to gain an insight of the meanings, views and opinions of the interviewee. The latter allows to allow the researcher to build on insights drawn from the interview in terms of the research area being addressed.^38^

Findings from interviews and feedback from participants and clinicians will be used after the 1st cycle of recruitment to inform changes to the intervention and processes for the 2nd cycle of recruitment. This will be repeated for the 2nd recruitment cycle to inform the 3rd cycle of recruitment. In this way it is envisaged that at the end of the 3rd and final cycle, the processes, intervention and design will be ready to form the basis of a full RCT. Changes will be made in discussion with the trial management group (TMG) and protocol amendments requiring ethical approval will be sought as appropriate. Subsequent interviews will be analysed by the researcher on an iterative basis, whereby, the ongoing analysis, along with the reflexive diary, will be used to identify new issues to explore with successive interviewees. Atlas.ti software will be used to manage the qualitative data.

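### The 20-week cycle leaves out the wait before physiotherapy, so full courses of late recruits, mostly in usual care, can run past the cycle and into a revised intervention, and no breakdown by cycle is named

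*Protocol article*

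**What the plan says.** The protocol article sets the timing in several places.

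- Design, Quantitative: "Recruitment will occur in three, 20-week cycles, illustrated in table 1". Within each cycle "there will be 12 weeks of active recruitment followed by up to 8 weeks for treatment to be completed". Between cycles, "A 2-week period between cycles will provide time to reflect and analyse on the results from the stakeholder interviews and other feedback".
- Abstract, Methods and analysis: "The usual care group will begin their physiotherapy 6 weeks after randomisation and the intervention group at 2 weeks after randomisation".
- The intervention: "Participants will receive up to six sessions of physiotherapy over an 8-week period or until they have achieved their predetermined goals".
- Qualitative analysis: interview findings and feedback "will be used after the 1st cycle of recruitment to inform changes to the intervention and processes for the 2nd cycle of recruitment". The same step is repeated between the second and third cycles.
- Data analysis plan: "Outcome measures will be summarised overall and by randomised group". Consent, recruitment and follow-up rates are reported by centre and by arm. Cycle is not named as a breakdown.
- Abstract, Ethics and dissemination: recruitment opened on 1 March 2016 and is expected to close in January 2017.

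Three further statements bear on the point. Both arms are treated under one framework (Randomisation), at one site (Setting), by three trained physiotherapists (Physiotherapist training and support).

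**The concern.** The 8 weeks after recruitment closes equal the maximum length of a course. They leave nothing for the time between randomisation and first session, which is the very thing the trial randomises. A full course for a late recruit therefore cannot end inside the cycle, and the excess is 4 weeks longer in usual care than in the intervention arm.

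This matters because the intervention may be revised twice, once at each boundary between cycles. The article does not say how a revision applies to a patient of the earlier cycle who is still in treatment. With one site and three physiotherapists delivering to both arms, carry-over is plausible, and any carry-over would fall more on usual care. If attendance, attrition and outcome summaries are then given only overall, by centre and by arm, the reader cannot see how far they describe a version that was later superseded. Those summaries are meant to inform the decision on a definitive trial.

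**Working it through.** **The plan's own figure.** 12 weeks of recruitment + 8 weeks of treatment = 20 weeks. This reproduces only if the last recruit starts treatment on the day of randomisation.

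**Inputs from the article.** Start delay: 2 weeks (intervention) or 6 weeks (usual care). Longest course: 8 weeks. Gap between cycles: 2 weeks, so the next cycle opens at week 22 if the gap is added to the 20 weeks. Total sample: 80.

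**Assumptions.** Recruitment is even over the 12 weeks, allocation is 1:1 (40 per arm), each cycle holds a third of the patients, and every course runs the full 8 weeks.

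**Formula.** A patient randomised at week t ends a full course at t + delay + 8:

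- intervention: t + 10, so the last recruit (t = 12) ends at week 22
- usual care: t + 14, so the last recruit ends at week 26

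Holding every full course would need 26 − 12 = 14 weeks after recruitment closes, not 8.

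**Share still in treatment at a boundary B.** This is the share of the 12 weeks in which t exceeds B − 8 − delay.

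| Boundary | Usual care | Intervention |
|---|---|---|
| Week 20 (end of cycle) | t > 6: 6/12 = 50% | t > 10: 2/12 = 17% |
| Week 22 (next cycle opens) | t > 8: 4/12 = 33% | t > 12: 0% |

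**Patients affected at week 22.** Only cycles 1 and 2 are followed by a revised version. Usual care: 40 × 2/3 × 1/3 = 8.9, about 9 of 40.

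**Sensitivity of the 0%.** The process objectives accept a first session up to day 20 in the intervention arm (for 75% of patients). Day 20 is 20/7 = 2.86 weeks, so the last course ends at 12 + 2.86 + 8 = week 22.9. The share past week 22 is then 0.86/12 = 7%, or 40 × 2/3 × 0.071 = 1.9, about 2 of 40.

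**Calendar.** Recruitment closes at 2 × spacing + 12 weeks after 1 March 2016:

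- spacing of 22 weeks: week 56, 28 March 2017
- spacing of 20 weeks: week 52, 28 February 2017
- closing by 31 January 2017 (week 48): spacing of at most (48 − 12)/2 = 18 weeks

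At 18-week spacing the boundary falls earlier. Usual care crosses it if t > 4 (8/12 = 67%) and intervention if t > 8 (4/12 = 33%).

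**Size of the overlap at 22-week spacing.** Usual-care patients who cross have between 0 and 4 weeks of course left, on average 2 of 8. As a share of usual-care treatment time this is 1/3 × 2/8 = 8.3% in cycles 1 and 2, and 2/3 × 8.3% = 5.6% over the trial.

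**Cost of splitting by cycle.** The approximate relative precision of an SD is 1.96/√(2(n − 1)). With about 72 measured patients (80 less 10%) it is 1.96/√142 = 16%, which matches the Sample size section. With 24 per cycle it is 1.96/√46 = 29%.

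**The case against.** Several objections have force.

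- **Mid-course change is not stated.** Revisions are tied to the next cycle of recruitment, which can be read as applying by recruitment cohort. On that reading nobody changes version during a course. This stands: the article is silent on the matter, and carry-over is a possibility rather than a plan.
- **The shares are upper limits.** A course may stop once goals are met. The section on primary and secondary outcome measures speaks of treatment starting within 2 and 6 weeks, so these times may be maxima. This stands too.
- **The contrast between arms is not clean.** A reader might infer that revisions reach usual care and never the intervention arm. The 0% needs every intervention patient to start by exactly week 2 and cycles to open 22 weeks apart. The day-20 tolerance and the January 2017 closing date support neither. Usual care nevertheless remains the more exposed arm in every scenario above.
- **Confounding of arm with version.** A reader might infer this, but it is too strong. Both arms recruit concurrently in every cycle, the third cycle has no successor, and the worst case at 22-week spacing is 5.6% of usual-care treatment time.
- **The end-of-cycle review.** A reader might infer that it lacks usual-care experience. About 10–15 interviews per arm are planned over three cycles, or 3–5 per cycle. Even on these assumptions 40/3 × 50% = 6.7 usual-care patients per cycle finish by week 20, and the interview analysis is iterative. That worry is not established.
- **Unseen material.** Table 1 is not shown and may give another layout, and a separate analysis plan may report by cycle. Neither removes the conflict between the cycle description, the start times and the course length as written.

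**Conclusion.** The timing statements do not fit together. The 20-week cycle omits a wait of 2 or 6 weeks, so full courses for the last recruits end 2 weeks (intervention) or 6 weeks (usual care) after the cycle does. With even accrual and full courses, up to 50% of usual-care and 17% of intervention patients are still in treatment at week 20. At 22-week spacing, up to a third of usual-care recruits in cycles 1 and 2 could still be in treatment when a revised intervention begins, against few or no intervention patients. The January 2017 closing date implies shorter spacing, which raises the overlap in both arms.

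What follows for the analysis is modest. Summaries that ignore cycle could mix versions, with any carry-over weighted towards usual care. The documents do not support calling the arm comparison confounded. Nor do they call for cycle as a term in an effect model, since none is named, or for planning from last-cycle SDs, which would rest on about 27 recruited patients. This is a point worth correcting because the pilot sets out to revise its intervention twice, but it does not undermine the pilot.

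**What to change.** 1. Reconcile the cycle length and gap (Design, Quantitative), the start times (Abstract, Methods and analysis), the course length (The intervention) and the recruitment dates (Abstract, Ethics and dissemination). This review does not say which timing is right.
2. State how a change made between cycles applies to patients still in treatment, by the same rule in both arms. The choice of rule is for the trial team.
3. Report the feasibility criteria and the main descriptive summaries by cycle of randomisation, beside the pooled values. Keep the pooled SD for sample-size planning.

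The cost is a few sentences and a few extra tables. The per-cycle estimates will be imprecise (about ±29% for an SD against ±16% pooled) and should be labelled descriptive.
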